## Abstract

**Background:**

Studies in heterosexual HIV serodiscordant couples have provided critical evidence on the role of HIV treatments and undetectable viral load in reducing the risk of HIV transmission. There is very limited data on the risk of transmission from anal sex in homosexual male serodiscordant couples.

**Methods/Design:**

The *Opposites Attract Study* is an observational prospective longitudinal cohort study of male homosexual serodiscordant partnerships running from 2012 to 2015 and conducted in clinics throughout Australia, Brazil and Thailand. Couples attend two or more clinic visits per year. The HIV-positive partner’s viral load is tested and the HIV-negative partner is tested for HIV antibodies at every clinic visit. Results from any tests for sexually transmitted infections are also collected. Detailed behavioural questionnaires are completed by both partners at the time of each visit. The primary research question is whether HIV incidence is lower in those couples where the HIV-positive partner is receiving HIV treatment compared to couples where he is not receiving treatment. A voluntary semen sub-study will examine semen plasma viral load in a subsample of HIV-positive partners in Sydney, Rio de Janeiro and Bangkok. In cases of seroconversion of the initially HIV-negative partner, phylogenetic analysis will be conducted at the end of the study on virus from stored blood samples from both partners to determine if the infection came from the HIV-positive study partner. Men in new serodiscordant relationships will specifically be targeted for recruitment.

**Discussion:**

This study will provide critical data on the reduction in HIV transmission risk associated with being on HIV treatment in homosexual male serodiscordant couples in different regions of the world. Data from men in new relationships will be particularly valuable given that the highest transmission risk is in the first year of serodiscordant relationships. Furthermore, the detailed behavioural and attitudinal data from the participant questionnaires will allow exploration of many contextual factors associated with HIV risk, condom use and the negotiation of sexual practice within couples.

## Background

Studies in heterosexual HIV serodiscordant couples have provided critical evidence on the role of HIV treatments and undetectable viral load in reducing the risk of HIV transmission. A number of observational studies, primarily in African heterosexual serodiscordant couples, have demonstrated a link between HIV treatment, undetectable viral load and reduced transmission risk
[1]. In 2011, the early results of a randomised clinical trial, HPTN 052, provided conclusive evidence that when the HIV-positive partner is on antiretroviral therapy (ART), transmission risk is dramatically reduced by 96% in heterosexual serodiscordant couples
[2].

The strategy of reducing HIV transmission risk by placing the HIV-positive partner on ART irrespective of stage of HIV infection has widely become known as ‘treatment as prevention’ (TasP)
[3–5]. Despite several studies demonstrating the effectiveness of TasP in heterosexual serodiscordant couples, there is currently no conclusive evidence on the relationship between ART and transmission in male homosexual serodiscordant couples
[6, 7]. Given that the risk of HIV transmission via anal intercourse is about 10 times greater than for vaginal intercourse
[8], it cannot be assumed that the effectiveness of TasP will be identical for the two types of sex. As anal intercourse is not uncommon among heterosexuals (for example, 20.9% of adult heterosexual men and 15.1% of adult heterosexual women in Australia report anal sex in their lifetime
[9]), findings in homosexual men may also have broader relevance for the effectiveness of TasP in heterosexuals.

Internationally, only one study has reported findings on TasP in homosexual male serodiscordant couples: the *Partners of people on ART – a New Evaluation of the Risks (PARTNER) Study* in the United Kingdom and Europe
[7]. The interim analysis presented in early 2014 provided promising but not yet conclusive results. Amongst 308 homosexual male serodiscordant couples, no phylogenetically linked HIV transmissions were observed in two years of follow-up. However, the results were statistically consistent with a possible risk of up to 1.17% per year for couples who reported any unprotected anal intercourse (UAI), and up to 1.97% per year in those couples where receptive UAI (with or without ejaculation) was reported
[10].

### Research questions

The *Opposites Attract Study* addresses the following questions, in serodiscordant male homosexual partnerships:Is HIV incidence lower in those couples where the HIV-positive partner is receiving ART, compared with not receiving ART?Is HIV incidence higher in those couples where the HIV-positive partner has detectable blood plasma viral load (BPVL) compared to those couples where he has undetectable BPVL?Is BPVL used in negotiating unprotected anal intercourse within couples?Is HIV transmission possible when the HIV-positive partner has undetectable BPVL but either partner has a relevant sexually transmitted infection (STI)?In a subsample of couples, is HIV incidence related to semen plasma viral load (SPVL) in the HIV-positive partner?In a subsample of HIV-positive men, is BPVL associated with SPVL?

## Methods/Design

### Summary of study design

*Opposites Attract* is an observational prospective longitudinal cohort study of male homosexual serodiscordant partnerships, coordinated by the Kirby Institute at the University of New South Wales, Australia. The study is conducted through several high HIV caseload clinics throughout Australia and in Bangkok, Thailand and Rio de Janeiro, Brazil. The study involves attendance at two or more clinic visits per year followed by completion of online computer-assisted self-interviews after each visit. At clinic visits, data are collected on HIV BPVL and CD4 T-cell count in the HIV-positive partner, HIV antibodies in the HIV-negative partner, and STI test results in both partners. Samples of blood for storage of plasma, serum and buffy coat are taken from both partners at baseline, once a year during follow-up (from the HIV-positive partner only), and at seroconversion of the initially HIV-negative partner should that occur. Anal swabs are taken for storage from the HIV-negative partner at baseline and if seroconversion occurs. In a voluntary sub-study at sites in Sydney, Bangkok and Rio de Janeiro, HIV-positive partners attending clinics are invited to provide a semen sample at the time of each clinic visit. Enrolment commenced in April 2012 and under current funding arrangements, follow-up will continue until the end of 2015.

### Sample size

The sample size calculations were based on the hypotheses relating to BPVL and HIV incidence. The calculations were performed using data on HIV incidence in HIV-negative men with HIV-positive primary regular partners from previous Kirby Institute studies
[11, 12]. It was not possible to be as precise in estimating the study’s power to test hypotheses concerning SPVL. Two types of power calculation were performed, to consider situations in which either zero or at least one linked seroconversion occur in the study. This was because the study may or may not identify cases of linked HIV transmissions within the serodiscordant couples.*At least 1 phylogenetically linked HIV seroconversion is identified in the cohort:*

We examined various plausible scenarios where the study would have at least 80% power to detect at least a 75% reduction in the incidence of HIV cases in those whose partners have undetectable as compared to detectable BPVL. For the primary power calculation, based on Australian research we assumed that 60% of HIV-positive partners will have undetectable BPVL
[13]. We also assumed that the HIV incidence in HIV-negative men whose partners have detectable BPVL will be 5.0 per 100 person-years. This assumption was derived from the incidence observed in the *Health In Men (HIM)* study, our previous cohort study of HIV-negative gay men in Sydney conducted between 2001 and 2007
[12]. The incidence of HIV in negative men whose partners had detectable viral load could not be directly calculated in the *HIM* study due to lack of completeness of data on the BPVL of HIV-positive partners. However, we estimated an incidence of around 5 per 100 person-years in partnerships where the HIV-positive partner had detectable BPVL. This was based on two factors: the HIV incidence of 2.2 per 100 person-years in men with HIV-positive primary regular partners in *HIM*
[14], and the fact that in 60% of these relationships, the BPVL would have been undetectable and therefore have lower HIV incidence than 2.2 per 100 person-years. In this scenario, we estimated 18 incident HIV infections would be required, requiring a total of 631 couple-years of follow-up to enable 80% statistical power to detect at least a 75% reduction in HIV incidence in men whose partners have undetectable BPVL.

For other scenarios we assumed greater proportions of HIV-positive partners with undetectable viral load. This was based on the possibility that more HIV-positive men may commence treatment following the publication of results from TasP studies in heterosexuals. These scenarios and the associated sample sizes are presented in Table 
1. In summary, a sample size of 640 couple-years of follow-up will result in a statistical power of approximately 80% even if the proportion of HIV-positive partners with undetectable BPVL increases to 70% or 80%. However, if this proportion increases to 90% of HIV-positive men, the study will be powered to detect an 80% reduction in HIV incidence in negative men whose partners have undetectable BPVL, which means the HIV incidence in these men will be 1.0 per 100 person-years or lower.2.*No phylogenetically linked HIV seroconversions are identified in the cohort (transmission rate = 0 per 100 person-years):*

As mentioned, recent research findings relating to the effectiveness of TasP
[2, 10] may lead to a greater percentage of HIV-positive gay men in serodiscordant relationships electing to receive ART and thus having undetectable BPVL. For the purposes of this calculation, we have assumed that this may increase to 80% or 90% of all serodiscordant couples. If this is the case, and if effective antiretroviral treatment is as successful at reducing the risk of HIV transmission in gay men as was found among heterosexuals in HPTN 052 (i.e. 96% reduction), we may find no phylogenetically linked seroconversions in this study. In this case, the analysis will focus on calculating the upper limit of the confidence interval of an HIV incidence of 0 per 100 person years in couples where the HIV-positive partner has undetectable BPVL.

Assuming that the study achieves 640 couple-years of follow-up, and no phylogenetically related transmissions are documented, the upper limit of the 97.5% single-sided HIV incidence in partnerships where the HIV-positive partner has undetectable BPVL would be 0.72 and 0.64 per 100 person-years, if the proportion of HIV-positive participants with undetectable BPVL is 80% and 90% respectively.

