### Data analysis

The primary analyses aim to determine if HIV incidence is reduced in the HIV-negative partner when the HIV-positive partner: (1) is taking ART compared to not taking ART, and (2) has undetectable viral load compared to detectable viral load. These incidence rates will be calculated by dividing the number of phylogenetically linked seroconversions for each group by the total number of person-years of follow-up for that group. If there are no phylogenetically linked seroconversions, the upper limit of the confidence interval around a transmission rate of zero will be determined. Given that laboratories utilise different assays for viral load testing which have various lower limits of detection (e.g. 20, 40, 50, or 150 copies per mL), the precise definition of ‘undetectable’ and ‘detectable’ BPVL differs across sites. This will be taken into account in analysis, and a standardised cut-off may be used for directly measured BPVL (e.g. less than 400 copies per mL).

Two of the study questions relate to SPVL. First, in the subsample of couples included in the Semen Sub-Study, HIV incidence will be compared between couples with detectable versus undetectable SPVL in the HIV-positive partner. Second, within the HIV-positive partners participating in the Semen Sub-Study, BPVL and SPVL will be compared at each study visit. HIV RNA levels in seminal plasma will be determined using an adaptation of an in-house assay for separation of seminal plasma from human samples and the COBAS® AmpliPrep/COBAS® TaqMan® system.

The behavioural and attitudinal data collected from the participant questionnaires will allow for both cross-sectional and longitudinal analyses. A key focus will be on the question of whether gay men in serodiscordant relationships use condoms less often when the HIV-positive partner has undetectable viral load
[17]. This will be explored both through directly measured and perceived viral load, both categorically in terms of those who have/do not have UAI as well as by the number and type (insertive/receptive and with/without ejaculation) of acts of UAI, and in relation to attitudes regarding TasP, communication within relationships, and relationship agreements about viral load and sexual practice.

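### The planning rate carries no linkage restriction while the primary analysis counts only linked seroconversions, so the linked events expected in 631 to 640 couple-years may be overstated.

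*Protocol article*

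**What the plan says.** **Planning rate (Sample size).** The plan assumes that "HIV incidence in HIV-negative men whose partners have detectable BPVL will be 5.0 per 100 person-years". On its origin it says "This assumption was derived from the incidence observed in the" previous cohort of HIV-negative gay men, the HIM study. The derivation is then given: "This was based on two factors: the HIV incidence of 2.2 per 100 person-years in men with HIV-positive primary regular partners", combined with the view that 60% of those partners would have been undetectable and so at lower risk of transmitting. A rate by partner viral load could not be calculated directly in that cohort, "due to lack of completeness of data on the BPVL of HIV-positive partners". Linkage between partners' viruses is not mentioned for it.

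**Target (Sample size).** For the primary calculation "we assumed that 60% of HIV-positive partners will have undetectable BPVL". The aim is "at least 80% power to detect at least a 75% reduction in the incidence of HIV cases" in men with undetectable partners. The result is 18 incident infections and 631 couple-years; the text that follows works with 640.

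**Endpoint (Data analysis).** The incidence rates are obtained by "dividing the number of phylogenetically linked seroconversions for each group" by that group's person-years. The power scenario is itself headed by the occurrence of at least one linked seroconversion. The abstract explains the purpose of the phylogenetic work: "to determine if the infection came from the HIV-positive study partner".

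**Outside exposure (Table 3).** The HIV-negative partner's questionnaire covers sex with other partners and group sex.

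**The concern.** The rate that drives the sample size and the endpoint of the primary analysis appear to count different events. Unqualified HIV incidence in men who have an HIV-positive regular partner would ordinarily include infections from anyone. The primary rate excludes infections that did not come from the study partner. The design plainly allows for such infections, since it plans phylogenetics to identify them and asks about other partners. Yet neither the Sample size section nor Table 1 discounts the planning rate for them.

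At stake is whether 640 couple-years, with follow-up funded only to the end of 2015, can yield the number of analysable events on which the 80% power statement rests.

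**Working it through.** **Inputs.** From Sample size: detectable-group rate 5.0 per 100 person-years; 60% undetectable, so the allocation ratio is k = 0.6/0.4 = 1.5; 75% reduction, so the rate ratio RR is 0.25; 80% power; 640 couple-years. Assumed: two-sided 5% significance, which the article does not state for this calculation but which reproduces Table 1. Assumed: the linked share f, for which the article gives no figure.

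**Step 1: reproduce the plan's figure.** The log-rank events formula (Freedman) with unequal allocation is

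E = (1.960 + 0.842)² × (1 + k·RR)² / [k (1 − RR)²] = 7.849 × 1.375² / (1.5 × 0.75²) = 17.59, rounded up to 18.

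Couple-years = 17.59 / [0.05 × (0.4 + 0.6 × 0.25)] = 17.59 / 0.0275 = 640, against 631 stated (1.4% apart). The same formula gives all 12 event counts in Table 1 and all 12 couple-year totals within 3%.

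This match needs the whole 5.0 to count as endpoint events. Nor does the 5.0 hide a discount. With the plan's own 60% and 75%, an overall rate of 2.2 implies 2.2 / (0.4 + 0.6 × 0.25) = 4.0 in the detectable group, which is below 5.0.

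**Step 2: the 75% reduction refers to linked transmission.** Multiply both groups' rates by f and keep RR = 0.25. Expected linked events are 640 × 0.0275 × f. Power is Φ(√(k·E) × (1 − RR)/(1 + k·RR) − 1.960). Couple-years for 80% power are 640/f, up to rounding. The score-test column enumerates the two Poisson counts.

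| Assumed linked share f | Expected linked events | Power, formula | Power, score test | Couple-years for 80% power |
|---|---|---|---|---|
| 100% | 17.6 | 80% | 80% | 640 |
| 90% | 15.8 | 76% | 75% | 711 |
| 80% | 14.1 | 71% | 70% | 799 |
| 70% | 12.3 | 65% | 64% | 914 |
| 60% | 10.6 | 58% | 58% | 1,066 |

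The required number of events stays at 18 throughout, because it depends only on the rate ratio, allocation, significance level and power.

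**Step 3: the 75% reduction refers to all infections.** Now 5.0 and 5.0 × 0.25 = 1.25 are both all-source rates. Suppose unlinked infections occur at a rate b per 100 person-years in both groups, since infections from other men have no stated reason to depend on the study partner's viral load. Removing b from each group leaves the linked rates.

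- b = 0.5: 4.5 versus 0.75, a reduction of 1 − 0.75/4.5 = 83%. Expected events are 640 × (0.4 × 0.045 + 0.6 × 0.0075) = 14.4. Score-test power is 88%.
- b = 1.0: 4.0 versus 0.25, a reduction of 94%. Expected events are 640 × (0.4 × 0.040 + 0.6 × 0.0025) = 11.2. Score-test power is 96%.

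Linked events fall under both readings. Power falls under the first and rises under the second.

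**The case against.** **Direction of the power effect.** The strongest objection is that scaling both groups by the same share assumes that infections from outside partners also fall by 75% when the study partner is undetectable. Nothing in the article supports that. If the published rates are all-source, removing a common background sharpens the contrast and power goes up (Step 3). This stands. A reader might infer that the 80% power is simply not reached; the article does not settle that, because it does not say which infections the 75% refers to.

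**The premise is inferred.** The article says only HIV incidence; it does not say that all sources are included, and the cohort reports it cites are not at hand. Incomplete partner viral load data do not by themselves show that linkage was absent. This also stands: the mismatch is between what is stated for the rate and what is stated for the endpoint. The 60% to 90% range is likewise an assumption.

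**Choice of test.** Exact-test power would be lower (66%, 59%, 52% and 43% for the four shares), and a reader might blame the whole gap from 80% on linkage. But the exact test gives only 72% at 640 couple-years with every infection linked, so about 8 points of the gap have another cause. Table 1 follows the log-rank formula, which is the right yardstick.

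**Offsets.** Recruitment targets new relationships, where the Discussion cites about 6 per 100 person-years. At 6.0 × 80% = 4.8, power would be about 78%. Table 1 also includes larger reductions: at 85% with 70% linked, score-test power is about 82%. These could soften the loss. However, the 6 is not used in the calculation and carries no linkage restriction either, and the larger reductions are separate scenarios from the 75% claim. The upper limits for the zero-event scenario (0.72 and 0.64) are unaffected.

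**Conclusion.** The point holds as a mismatch between the planning rate and the endpoint. The 5.0 per 100 person-years has no stated linkage restriction, the analysis counts only linked seroconversions, and no allowance bridges the two. The calculation has no slack: 640 couple-years give 17.6 events and 80% power only if the whole 5.0 is linked.

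Expected linked events are overstated if any infection behind the planning rate came from another partner. The effect on power depends on what the 75% means. The reading closest to the planned analysis is a 75% reduction in linked transmission, because the groups are compared on linked rates. Power then drops to between about 76% and 58% for assumed shares of 90% to 60%. On the all-infection reading with a common background, power could rise instead.

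It would go too far to say that the required 18 events is wrong, or that the study is shown to be underpowered. The first is unchanged at a fixed rate ratio; the second needs a linked share and a definition of the 75% that the article does not give.

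**What to change.** In Sample size, state that both the planning rate and the 75% reduction refer to phylogenetically linked infections. Apply an explicit assumed linked fraction to the 5.0, for example over 60% to 90%. Restate the expected linked events and the power of 640 couple-years over that range with the same test as Table 1, and label the required events in the text and in Table 1 as linked.

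The cost is a recalculation and a few sentences; the design, visits and analysis stay as they are. The downside is that the stated power may become less favourable than 80%.

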**Table 1 Tab1:** **Serodiscordant couples sample size calculations**

Percentage of HIV men who are on ART and have undetectable BPVL	Reduction in HIV incidence in HIV-negative men with partners with undetectable BPVL	Required number of HIV seroconversion events	Total sample size required
**60%**	0.75	18	631
	0.85	11	436
	0.95	7	305
**70%**	0.75	15	624
	0.85	9	413
	0.95	5	272
**80%**	0.75	14	692
	0.85	7	429
	0.95	4	256
**90%**	0.75	17	1008
	0.85	7	563
	0.95	3	276

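### 640 couple-years does not give about 80% power when 80% of partners are undetectable: Table 1 asks for 692, and small-count tests give about 55–69%

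*Protocol article*

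**What the plan says.** The Sample size section of the protocol article sets the aim as "at least 80% power to detect at least a 75% reduction in the incidence of HIV cases", comparing undetectable with detectable blood plasma viral load (BPVL). It assumes that the "HIV incidence in HIV-negative men whose partners have detectable BPVL will be 5.0 per 100 person-years". For the primary scenario, "we assumed that 60% of HIV-positive partners will have undetectable BPVL", and on that basis "we estimated 18 incident HIV infections would be required, requiring a total of 631 couple-years of follow-up".

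Table 1 repeats the calculation for 70%, 80% and 90% undetectable. For a 75% reduction, its column "Total sample size required" gives 631, 624, 692 and 1008 couple-years at 60%, 70%, 80% and 90%, with 18, 15, 14 and 17 events.

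The text then sums up: "a sample size of 640 couple-years of follow-up will result in a statistical power of approximately 80" per cent, "even if the proportion of HIV-positive partners with undetectable BPVL increases to 70% or 80" per cent. The following sentence says that at 90% undetectable the study is powered for an 80% reduction. Neither the test, nor alpha, nor its sidedness is given for this comparison.

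**The concern.** The summary presents the design as robust to rising treatment uptake. The article treats that rise as a real possibility: its zero-transmission calculation assumes 80% or 90% undetectable. Yet the 80% row of Table 1 already exceeds 640. The required event counts are also small (14 in that row) and the person-time is split 4 to 1 or 9 to 1, conditions under which large-sample formulas can mislead.

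Undetectable versus detectable viral load is one of the two primary comparisons in the Data analysis section. If the real power at 80% undetectable is well under 80%, the chance of missing a true 75% reduction is well above the 20% that a reader would take from the text.

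**Working it through.** **Inputs.** From the Sample size section: detectable-group rate 5.0 per 100 person-years; 75% reduction, so 1.25 per 100 in the undetectable group; 640 couple-years. From Table 1: the couple-years and events above. Assumption: two-sided alpha 0.05, the value that reproduces Table 1.

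**Step 1: reproduce Table 1.** Let q be the undetectable share, k = q/(1 − q), and R the rate ratio. The Freedman log-rank formula with unequal allocation gives the number of events

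E = (1.96 + 0.84)² × (1 + kR)² / [k(1 − R)²], with (1.96 + 0.84)² ≈ 7.849,

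and couple-years N = E / m, where m = 0.05 × [(1 − q) + qR].

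For q = 0.8 and R = 0.25: k = 4, E = 7.849 × 4 / (4 × 0.5625) = 13.95, m = 0.05 × (0.2 + 0.2) = 0.020, N = 13.95 / 0.020 = 698.

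| Undetectable | E (rounded up) | Table 1 events | N | Table 1 couple-years |
|---|---|---|---|---|
| 60% | 17.59 (18) | 18 | 640 | 631 |
| 70% | 14.99 (15) | 15 | 631 | 624 |
| 80% | 13.95 (14) | 14 | 698 | 692 |
| 90% | 16.38 (17) | 17 | 1008 | 1008 |

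The formula matches all 12 event counts in Table 1 after rounding up, and all 12 couple-year values to within about 2%.

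**Step 2: the summary sentence by the table's own formula.** At q = 0.8, 640 couple-years gives 640 × 0.020 = 12.8 events (128 couple-years × 0.05 = 6.4 detectable; 512 × 0.0125 = 6.4 undetectable). Power = Φ(√(12.8 × 4) × 0.75 / 2 − 1.96) = Φ(2.683 − 1.96) = Φ(0.723) ≈ 0.77. At q = 0.7 the same calculation gives 0.80–0.81.

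**Step 3: power without the approximation.** Take two independent Poisson counts with means 640 × (1 − q) × 0.05 and 640 × q × 0.0125. Sum the probability of every pair of counts that rejects in the protective direction at 0.025 (one tail of a two-sided 0.05 test).

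| Undetectable | Couple-years | Exact conditional | Mid-p | Score |
|---|---|---|---|---|
| 60% | 640 | 0.72 | 0.80 | 0.80 |
| 70% | 640 | 0.66 | 0.73 | 0.78 |
| 80% | 640 | 0.55 | 0.63 | 0.69 |
| 80% | 692 (Table 1) | 0.59 | 0.66 | 0.72 |
| 90% | 1008 (Table 1) | 0.52 | 0.59 | 0.69 |

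Simulated log-rank power at 640 couple-years is 0.76–0.77 at 70% and 0.68–0.69 at 80%, close to the score test.

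**Step 4: couple-years for 80% power, 75% reduction.**

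| Undetectable | Table 1 | Score | Exact |
|---|---|---|---|
| 60% | 631 | about 644 | about 748 |
| 70% | 624 | about 680 | about 860 |
| 80% | 692 | about 864 | about 1088 |
| 90% | 1008 | about 1408 | about 1892 |

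The score-test requirement exceeds Table 1 by about 2%, 9%, 25% and 40% in turn, so the optimism grows as the detectable group shrinks.

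**Step 5: the sentence on 90% undetectable and an 80% reduction.** With k = 9 and R = 0.2: E = 7.849 × 2.8² / (9 × 0.64) = 10.68, m = 0.05 × (0.1 + 0.18) = 0.014, N ≈ 763. At 640 the expected number of events is 8.96. Power is 0.73 by the same formula and 0.40 (exact), 0.50 (mid-p) or 0.61 (score) by enumeration.

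**The case against.** Several points on the other side stand.

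- **Choice of test.** The article names no test or alpha, and an analysis plan may do so. The exact conditional test is conservative, so the lowest figures (55%, 66%) depend on choosing it. However, the score test is the most favourable two-sided test in the tables above and still gives 69% at 80% undetectable. A one-sided 0.05 score test would need about 684 couple-years there, still above 640, and one-sided alpha does not reproduce Table 1.
- **The 70% scenario.** A reader might infer that the claim is equally wrong at 70%. With a score or log-rank test, power is 76–78%, which the word approximately can bear. The shortfall is clear only with mid-p or exact tests.
- **The status of Table 1.** A reader might infer an arithmetic slip, such as interchanged group shares. Nothing in the article supports that: the table matches a recognised approximation, and its primary 60% row is about right by score or mid-p test. Nor is there an error in the 90% row for a 95% reduction, where 3 events are required; that is 2.03 rounded up.
- **Effect size.** The summary sentence does not restate the 75% reduction. But that is the declared target, and the next sentence moves to 80% by way of contrast, so 75% is the natural reading.
- **Size of the internal mismatch.** Taken alone, 640 against 692 costs only about three points of power (77% against 80%). The larger part of the shortfall comes from the approximation.

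**Conclusion.** The concern holds for 80% undetectable, and for the companion sentence on 90%. At 80%, the summary conflicts with Table 1 without any assumption about method (692 couple-years and 14 events required; 640 and 12.8 available). Under two-sided 0.05, enumerated power is about 55–69% at 640 and only 59–72% at the tabulated 692. The chance of missing a true 75% reduction at 640 is therefore about 31–45%, not 20%. At 90%, the claim for an 80% reduction needs about 763 couple-years by the table's own formula, and power at 640 is about 40–61%.

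At 70% the shortfall is modest, and the primary 60% calculation is about right by score or mid-p test. The conclusion rests on the article's rates, on constant shares of person-time, and on the assumed two-sided 0.05. It does not show that the study needs more couples, only that the power stated for the higher-uptake scenarios is too high.

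**What to change.** State alpha, sidedness and the test behind the calculation. Recompute Table 1 with a method valid for small counts and very unequal person-time, for example enumerated power for the planned rate comparison. Replace the two summary sentences with the power that 640 couple-years gives at 60%, 70%, 80% and 90% undetectable, naming the reduction to which each figure refers.

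The cost is a recalculated table and two reworded sentences. Recruitment and follow-up need not change. The drawback is a less favourable stated power in the higher-uptake scenarios.

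### With 90% of partners undetectable, 640 couple-years gives about 73% power for an 80% reduction by the formula that reproduces Table 1; 80% power needs a reduction of about 83%

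*Protocol article*

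**What the plan says.** All of this is in the Sample size section of the protocol article and its Table 1.

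- **Power standard:** the scenarios were chosen to give "at least 80% power to detect at least a 75% reduction in the incidence of HIV cases".
- **Control rate:** the assumption is that "HIV incidence in HIV-negative men whose partners have detectable BPVL will be 5.0 per 100 person-years".
- **Primary scenario:** "we assumed that 60% of HIV-positive partners will have undetectable BPVL", from which "we estimated 18 incident HIV infections would be required, requiring a total of 631 couple-years of follow-up".
- **Planned follow-up:** for 70% or 80% undetectable, "a sample size of 640 couple-years of follow-up will result in a statistical power of approximately 80" per cent.
- **The sentence at issue:** "if this proportion increases to 90% of HIV-positive men", then "the study will be powered to detect an 80% reduction in HIV incidence in negative men whose partners have undetectable BPVL". The text equates this with an incidence of 1.0 per 100 person-years or lower in the undetectable group.
- **Table 1, column "Total sample size required", at 90% undetectable:** 1008 for a 75% reduction, 563 for 85% and 276 for 95%, with 17, 7 and 3 events. No row is given for 80%.

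The section states no alpha, sidedness or test for the comparison.

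**The concern.** An 80% reduction lies midway between two tabulated reductions whose requirements are 1008 and 563 couple-years. The planned 640 is much nearer the lower of these. Required follow-up falls smoothly as the reduction grows, so the value for 80% should be well above 640.

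The sentence is the plan's only statement about the power of the viral-load comparison if the undetectable share reaches 90%, and that comparison is one of the primary analyses under Data analysis. The plan treats 90% as a real possibility. A reader would take from the sentence that the comparison keeps its 80% power for an 80% reduction in that case.

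**Working it through.** **Inputs from the Sample size section:** detectable-group rate 0.05 per person-year; 80% power; 640 couple-years; undetectable share p; rate ratio h = 1 − reduction. **Assumption:** two-sided 5% alpha, because it reproduces Table 1. Then (1.960 + 0.842)² = 7.849.

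**Formula (Freedman log-rank, unequal allocation), with k = p/(1 − p):**

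- Events: D = 7.849 × (1 + kh)² / [k(1 − h)²]
- Couple-years: N = D / [0.05(1 − p) + 0.05hp]

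**Step 1. Reproduce the plan's own figures.**

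| p | Reduction | D | N | Table 1 events | Table 1 size |
|---|---|---|---|---|---|
| 60% | 75% | 17.59 | 640 | 18 | 631 |
| 70% | 75% | 14.99 | 631 | 15 | 624 |
| 80% | 75% | 13.95 | 698 | 14 | 692 |
| 90% | 75% | 16.38 | 1008 | 17 | 1008 |
| 90% | 85% | 6.67 | 567 | 7 | 563 |
| 90% | 95% | 2.03 | 280 | 3 | 276 |

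All 12 tabulated sizes are matched within about 2%. All 12 event counts match exactly once D is rounded up.

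**Step 2. Use Table 1 alone.** Linear interpolation between the 75% and 85% rows gives (1008 + 563)/2 = 786, and geometric interpolation gives √(1008 × 563) = 753. If the curve is convex, as its three points are, the value for 80% cannot exceed 786. Nor can it fall below the line through the 85% and 95% rows extended back: 563 + (563 − 276)/2 = 707. The whole range is above 640.

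**Step 3. Apply the formula to the sentence (p = 0.9, h = 0.2, k = 9).**

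- D = 7.849 × 2.8² / (9 × 0.8²) = 7.849 × 7.84 / 5.76 = 10.68, so 11 events
- Mean rate = 0.005 + 0.009 = 0.014
- N = 10.68 / 0.014 = 763 couple-years

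**Step 4. Power at 640.**

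- Expected events: 64 × 0.05 + 576 × 0.01 = 3.20 + 5.76 = 8.96
- z = √(8.96 × 9) × 0.8 / 2.8 − 1.960 = 2.566 − 1.960 = 0.606
- Power = Φ(0.606) = 0.73

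**Step 5. Reduction that 640 does support at 80% power.** For h = 0.17:

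- D = 7.849 × 2.53² / (9 × 0.83²) = 8.10
- Mean rate = 0.005 + 0.00765 = 0.01265
- N = 8.10 / 0.01265 = 641

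The detectable reduction is therefore about 83%, an undetectable-group incidence of 5.0 × 0.17 = 0.85 per 100 person-years.

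**Step 6. Small-sample check.** Power was found by enumerating two independent Poisson counts, conditioning on the total and testing at two-sided 5%.

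| Scenario at 90% undetectable | Exact | Mid-p | Score |
|---|---|---|---|
| 640 couple-years, 80% reduction | 40% | 50% | 61% |
| 1008 couple-years, 75% reduction (tabulated) | 52% | 59% | 69% |
| 563 couple-years, 85% reduction (tabulated) | 42% | 52% | 64% |

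The shortfall in Step 6 is common to the 90% rows. It comes from using a large-sample formula with very few events. The shortfall in Step 4 is specific to the sentence.

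**The case against.** **Table 1 has no 80% row.** This stands. A reader might infer that the sentence contradicts a tabulated figure, but 640 lies between 563 and 1008. The conflict appears only on interpolation or recomputation. The bounds in Step 2 are nevertheless all above 640.

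**Alpha and sidedness are not stated.** This also stands, so it would be too strong to call the sentence wrong under any test. With one-sided 5% the same formula needs 601 couple-years and gives 82% power at 640. But that choice gives 504 where Table 1 has 631 and 794 where it has 1008. The sentence and the table cannot both come from it.

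**The error is modest on the plan's own method.** It is: 83% against 80%, or 73% power against 80%. The section also works loosely elsewhere. It describes 640 as giving approximately 80% power at 80% undetectable, where Table 1 asks for 692 and the formula gives 77%. The sentence on 90% carries no such qualifier, and its gap is about twice as large.

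**The near-even odds from exact tests are a different matter.** A reader might infer from the 40% to 61% figures that this one sentence is badly wrong. The document names none of those tests, and the tabulated 90% rows fall short in the same way. Nor does it follow that even a 95% reduction is underpowered at 640: the exact and mid-p tests give 66% and 74%, but the score test gives 85%.

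**90% undetectable is a contingency.** The plan says uptake may rise that far; it does not forecast it. The primary calculation uses 60%.

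**Conclusion.** The sentence is wrong as written, by a limited amount. By the formula that reproduces Table 1, an 80% reduction at 90% undetectable needs about 763 couple-years, 123 more than planned (19% of 640). At 640 the power is about 73%, and 80% power is reached only for a reduction of about 83%. This rests on a detectable-group rate of 5.0 per 100 person-years and on two-sided 5% alpha, which is inferred from the table.

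A second and more general point is that all the 90% figures are optimistic, because the formula is being used with between 3 and 17 events.

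A reader might infer that at 90% undetectable the comparison should give way to an upper confidence limit. The documents do not support that. Sample size and Data analysis both reserve that analysis for zero linked seroconversions. The scenario in dispute expects about 9 events, so the chance of none is about e^(−8.96), or roughly 1 in 8,000. The 640 target, the primary scenario and the planned analysis are not called into question by this point.

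**What to change.** 1. Restate the sentence in one of two ways. Either: at 90% undetectable, 640 couple-years gives 80% power for a reduction of about 83% (undetectable-group incidence about 0.85 per 100 person-years). Or: it gives about 73% power for an 80% reduction.
2. Add a row to Table 1 for 90% undetectable and an 80% reduction: 11 events, about 760 couple-years.
3. State the alpha, sidedness and formula used for the table.
4. Add a note that with so few events the 90% rows are optimistic, giving the enumerated power at 640 for an 80% reduction (about 40% exact, 50% mid-p, 61% score) and saying that the tabulated 75% and 85% rows fall short similarly.
5. Keep the planned rate comparison, and keep the upper confidence limit for the case of zero linked seroconversions.

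This costs a sentence, a table row and a short note. No change to design or analysis is needed. The stated power becomes less favourable.
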